#### Exploratory analysis

A subgroup analysis of the participants in the intervention group will be conducted using different IM apps and data on referrals to treatment institutions to determine whether the relative effects of study treatments vary significantly among subgroups of IM app users. Propensity score matching, including demographics and types of abused drugs, will be used to further determine the true cause-and-effect relationship between the intervention and control groups, with restrictions of these subgroups. Missing outcomes will be assumed to be dependent on observed data (missing at random), and the observed data will be analysed with a multiple imputation procedure to impute the missing values, as a sensitivity analysis.

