### Participants and sampling

Callers to the MedPAC Quitline and those who are actively recruited from schools and communities will be eligible service targets for the MedPAC Quitline. Youth who misuse drugs and have contacted the MedPAC Quitline will be eligible for inclusion in this proposed study if they (1) are 25 years of age or younger, (2) report having taken drugs within the past 30 days, (3) are able to communicate in Chinese, (4) agree to receive counselling via a messaging app (such as WhatsApp or WeChat), and (5) verbally consent to join the follow-up intervention. We will exclude potential subjects who have communication barriers and those who are undergoing other drug-misuse recovery treatments.

Because no previous study has conducted a brief telephone-based MI intervention, the sample size for the proposed RCT has been calculated according to a previous RCT that involved a computer-based MI intervention [18]. In this previous RCT, the mean number of drug-misuse consumptions per day decreased from 11.94 at baseline to 5.52 at 12 months for participants in the intervention group, and 9.22 at baseline to 8.61 at 12 months for those in the control group. The effect size was 0.64 for the MI intervention on drug-misuse reduction, with reference to the control group [18]. Based on these results, to detect a two-sided significant difference between groups with a power of 80 % and a significance level of 5 %, which are commonly accepted metrics for behavioural studies, the required sample size for this proposed RCT has been estimated to be 40 participants in each group. Given an expected retention rate of approximately 60 % at the 12-month follow-up, the target number of participants will be at least 134 (67 per group).

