#### Control group

The subjects will receive general health information via text message, such as ‘do physical exercise for at least 30 minutes per week to keep yourself healthy’, for 6 months at a frequency of twice a week.

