Referral need and results	×	×	×	×	×	×	×

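### The messaging-app and referral subgroup analysis runs inside the intervention arm, so it cannot show whether the treatment effect varies, and the planned propensity matching does not repair this

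*Protocol article*

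**What the plan says.** The Exploratory analysis section of the protocol article describes two steps.

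- Step 1: "A subgroup analysis of the participants in the intervention group will be conducted using different IM apps and data on referrals to treatment institutions". Its purpose is to find out "whether the relative effects of study treatments vary significantly among subgroups of IM app users".
- Step 2: "Propensity score matching, including demographics and types of abused drugs, will be used to further determine the true cause-and-effect relationship". The section places this comparison "between the intervention and control groups, with restrictions of these subgroups".

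Other parts of the article bear on these steps:

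- **Control group**: "The subjects will receive general health information via text message". No app subgroup is described for controls.
- **Participants and sampling**: everyone must agree to counselling through a messaging app, with two given as examples. The article does not say that a named app is recorded before allocation.
- **Measures, Table 1**: the row "Referral need and results" is marked at baseline and at all six follow-ups (1 week to 12 months).
- **Resource and setting**: the quitline's own counsellors make the referrals, according to need.
- **Discussion**: further post hoc subgroups are planned on baseline pattern of use, dependence, readiness to quit and quit history.

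**The concern.** Step 1 asks a question about effect modification in a population that cannot answer it. With intervention participants only, a difference between users of two apps mixes any difference in treatment effect with any difference in prognosis, and nothing separates the two.

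Referral adds a second problem. Only the intervention arm has counsellor chat at least twice a week for 6 months, and that chat is meant to make participants aware of helping resources. The article's own rationale is that the intervention may increase help-seeking. Referral after allocation may therefore be partly a result of treatment, and referred participants in one arm need not resemble those in the other.

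Step 2 then attaches strong causal language to a matched comparison within these subgroups. At stake is the interpretation of secondary findings: a prognostic difference could be reported as one app working better, or a selected contrast as a causal effect.

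**Working it through.** **1. The plan's own figures.** Inputs from Participants and sampling: effect size 0.64, two-sided 5%, power 80%, retention about 60%.

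- n per group = 2 × (1.960 + 0.842)² / 0.64² = 38.3, so 39 by the normal formula. The t-test version gives 39.3, so 40.
- 40 / 0.60 = 66.7, so 67 per group and 134 in total.

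Both stated figures reproduce. Below, 40 per arm stands for completers and 67 per arm for all randomised participants.

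**2. What the within-arm test detects.** Assume no effect modification, but an app that is prognostic by d SD. The article gives neither d nor the app split, so both are assumptions. With share q on one app and N in the arm:

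- SE = sqrt[1/(Nq) + 1/(N(1−q))]. For N = 40 and q = 0.5, sqrt(1/20 + 1/20) = 0.316 SD.
- Rejection rate = Φ(d/SE − 1.96) + Φ(−d/SE − 1.96).

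| Split | N = 40, d = 0.3 to 0.64 | N = 67, d = 0.3 to 0.64 |
|---|---|---|
| 50/50 | 16% to 53% | 23% to 75% |
| 70/30 | 14% to 46% | 20% to 67% |
| 80/20 | 12% to 37% | 17% to 55% |

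Read as evidence that the effect varies, every one of these rejections is false. With d = 0 the rate is the nominal 5%.

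**3. What restriction to the subgroups does.** This was checked by a large simulation with a constant true effect of 0.64, an unmeasured severity factor related to app use, referral and outcome, and one measured covariate. The covariate was handled by regression adjustment, as a stand-in for matching on measured variables. The structure and strengths are assumed, so the results show the direction of the problem and do not predict its size in this trial.

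- App known only in the intervention arm, each app group set against all controls: apparent effects 0.39 and 0.89, although the true effect is 0.64 in both.
- Referral raised by the intervention (log odds ratio 0.7 to 1.4): effects of 0.70 to 0.77 in the referred and 0.70 to 0.75 in the non-referred. If the intervention does not change referral, both are 0.64.
- App known before allocation in both arms: 0.64 in both groups.

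**4. What a sound analysis could detect.** For an arm-by-app interaction with N per arm:

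- SE = sqrt[2/(Nq) + 2/(N(1−q))]. For N = 40 and q = 0.5, sqrt(2/20 + 2/20) = 0.447 SD.
- Smallest interaction detectable with 80% power = 2.80 × SE. For this case, 2.80 × 0.447 = 1.25 SD.

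| Split | Detectable, N = 40 | Detectable, N = 67 | Power for 0.64 SD, N = 40 | Power for 0.64 SD, N = 67 |
|---|---|---|---|---|
| 50/50 | 1.25 SD | 0.97 SD | 30% | 46% |
| 70/30 | 1.37 SD | 1.06 SD | 26% | 40% |
| 80/20 | 1.57 SD | 1.21 SD | 21% | 32% |

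Even an interaction as large as the planned main effect would more likely be missed than found.

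**The case against.** The strongest defence is that this section is labelled exploratory, that the plan fixes intention to treat for its analyses, and that step 2 does bring in the control group. Much of that stands, and it limits how far the point can be taken.

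- A reader might infer that neither step could ever estimate how the effect varies. The article does not support that. Step 2 compares the arms within subgroups, and could give app-specific effects if app choice were fixed before allocation in both arms, or depended only on the matched variables. The article states neither.
- A reader might infer that all subgroup effects are judged inside one arm. They are not: the subgroups in the Discussion are defined at baseline and are not restricted to one arm.
- A reader might infer that referral is purely a post-randomisation variable. Table 1 also has a baseline entry, and the section does not say which time-point defines the subgroup.
- A reader might infer that the matching must ignore motivation. The named variables are introduced as inclusions, so the list may be longer, and motivation is measured at baseline.
- A reader might infer that the matched result would outrank the intention-to-treat result. Nothing in the article says so.

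It can also be argued that, if restriction to a subgroup breaks randomisation, balancing covariates has a purpose. It has, but for later referral it helps only if every joint cause of referral and outcome is included, and even then the contrast leaves out any part of the effect that runs through referral.

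The exploratory label lowers the weight of a result. It does not supply a missing control group.

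**Conclusion.** The point holds for the app and referral subgroups. Step 1, as worded, cannot show whether the treatment effect varies. Subgroups formed on referral after allocation are not comparable between arms. Matching on demographics and drug types does not repair selection on app use or on later referral, and the causal wording is unsupported, since randomisation already gives the causal comparison between arms.

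The size depends on assumptions. At an even split, a purely prognostic app difference of 0.3 to 0.64 SD would lead the within-arm test to reject 16% to 53% of the time with 40 in the arm, or 23% to 75% with 67. The simulated biases rest on an assumed unmeasured severity factor.

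The point concerns only the exploratory section; the primary comparison is not affected. It rests on the population and purpose that the section states, not on detail that a fuller analysis plan might supply.

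**What to change.** - **App:** test an arm-by-app interaction in all randomised participants, using app preference recorded before allocation in both arms, and report estimates with confidence intervals. Where preference was not recorded before allocation, report app differences within the intervention arm as descriptive only. This may apply to early participants, because recruitment was due to begin in March 2021 and eligibility records agreement to a messaging app, not a named choice.
- **Referral:** use only baseline referral status as a subgroup. Report later referral by arm, as an outcome or process measure.
- **Matching:** delete the propensity-score matching and its causal wording.
- **Power:** state that the analysis is exploratory with low power. At an assumed even split the smallest interaction detectable with 80% power is about 1.25 SD with 40 per arm or 0.97 SD with 67 per arm, and larger if the split is uneven.

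The cost is one extra baseline field, revised wording and a little more analysis work. No change to the sample size or to the primary analysis is needed.

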#### Text mining of IM app group conversations

All interaction content will be archived and anonymised to remove identifying personal information. Due to the large number of messages that will be collected from the IM apps, we will use automatic, computational text-mining and visualisation of the dataset for the content analysis. First, using a lexicon of keywords derived from our qualitative analysis of the pilot RCT (unpublished), we will develop a heat-map visualisation to illustrate the prevalence of the discussion topics. Second, we will apply topic modelling to investigate emerging themes in our content dataset, using the Mallet [27] implementation of the Latent Dirichlet Allocation topic modelling algorithm [28]. Topic modelling algorithms use a text dataset (in this case, the content dataset) as input and then output a set of topics (and their associated keywords) in addition to estimates of the proportion of each topic [29].

## Discussion

Four caveats should be considered when the findings of this proposed study are interpreted. First, this pragmatic RCT will not guarantee ‘full’ intervention compliance by all participants. For instance, the participants in the intervention group will be encouraged to interact with the interventionists, but they will have the right to ignore the IMs. Thus, they will be able to choose to either respond to an interventionist or to remain silent throughout the intervention period. As a result, although the RCT will show the effectiveness of delivering such an interaction for drug-misuse cessation, we expect that there will be a variety of levels of participation in the interaction. Nevertheless, all IM conversations will be archived for further content analysis and compliance analysis. The actual effect of participating in an interaction will be investigated by filtering out participants who exhibit low participation. Second, we will only recruit drug-misusing youths in this RCT who have also enrolled in the MedPAC Quitline service, and thus the findings will not be generalisable to unassisted youths who misuse drugs. Future trials that customise the intervention for drug-misusing youths recruited from outside the service will be warranted. Third, recreational users, who are common among young people with substance use, will be also included in this trial. This could potentially limit the room for significant improvement. Considering recreational drug use is a common situation among the youth population, this group should not be ignored. To explore the effect of the intervention in the different participants with such use patterns, we will conduct post hoc analysis for subgroups of the pattern of use, dependence level, readiness to quit in the next 30 days, and previous quit history at baseline. Fourth, all measures will be self-reported. However, the validity of self-reported versus biochemical assessment of substance use may vary according to a variety of contextual factors. Evidence of the ability of existing biochemical methods to detect reductions in drug misuse remains scarce. Nevertheless, a previous study indicated that self‐report may outperform biological assessment for the assessment of patterns of drug use over the past month, because biological assessment typically only captures substance use that has occurred in the past 5 days [30].

The findings from this study will be disseminated locally and internationally through manuscript publications in peer-reviewed journals and conference presentations at national and international platforms. The proposed intervention has the potential to increase the help-seeking behaviour and intention to quit of youth who misuse drugs and are reluctant to seek help from services that require real-name registration. With such assistance, more youth may abstain from drug misuse. This proposed study will be the first RCT to assess the effectiveness of a medical peer-delivered, IM-based, interactive intervention in reducing drug misuse among youth in Hong Kong. Thus, this study will inform decisions on whether it is worthwhile to invest resources in large-scale implementation of such an intervention to reduce drug misuse in Hong Kong’s youth.

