### Data analysis

Data analysis will be performed using the Statistics Package for the Social Sciences (SPSS) version 25.0 for Windows (SPSS Inc., Chicago, IL, USA). Analyses will be conducted on an intention-to-treat basis, with missing-value substitutions based on the last observation carried forward. A two-sided statistical significance level of 0.05 will be adopted for all analyses.

Descriptive statistics will be used to detail participants’ demographic characteristics and drug misuse profiles. Frequencies and percentages or means and standard deviations will be used to present categorical data and continuous data, respectively. The differences between intervention and control groups, in terms of sociodemographic factors and outcomes, will be compared using a chi-square test for categorical variables and by an analysis of variance for continuous variables.

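### Filtering out low participators gives a non-randomised, self-selected contrast that should not be labelled the actual effect of participating

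*Protocol article*

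**What the plan says.** The first caveat in the protocol article's Discussion deals with uneven engagement. It states that "the participants in the intervention group will be encouraged to interact with the interventionists, but they will have the right to ignore the IMs", and that "they will be able to choose to either respond to an interventionist or to remain silent throughout the intervention period". It then commits to an analysis: "The actual effect of participating in an interaction will be investigated by filtering out participants who exhibit low participation". It gives no participation threshold, comparator or adjustment for this analysis.

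The Control group section describes a different exposure: "The subjects will receive general health information via text message", twice a week for 6 months. It describes no interaction on which a control could be classed as a low participator.

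The Data analysis section sets the main approach: "Analyses will be conducted on an intention-to-treat basis, with missing-value substitutions based on the last observation carried forward". The Exploratory analysis section adds: "Propensity score matching, including demographics and types of abused drugs, will be used to further determine the true cause-and-effect relationship". That matching belongs to the messaging-app and referral subgroups, and it names neither motivation nor readiness to quit.

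**The concern.** Someone who answers a counsellor's messages for months probably differs from someone who stays silent, and readiness to change is the obvious difference. It could drive both replying and cutting down. The protocol itself treats readiness as relevant. It measures contemplation stage and treatment motivation at baseline (Measures) and plans a post hoc subgroup by readiness to quit (Discussion). Neither is attached to the participation filter.

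Removing silent people from the intervention arm, with no counterpart removed from the control arm, undoes the balance that randomisation provided. The result would still carry a causal name. The same caveat separates the effect of delivering the intervention from the effect of taking part, and the article closes by saying that the study will inform large-scale implementation. A filtered estimate labelled as the actual effect could be given more weight there than it can bear.

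**Working it through.** **The plan's own figures.** The sample size section states: "The effect size was 0.64 for the MI intervention on drug-misuse reduction, with reference to the control group". With two-sided alpha 0.05, 80% power and SD set to 1:

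- Normal approximation: n = 2 × ((1.96 + 0.84) / 0.64)² = 38.3, so 39 per group.
- Exact t: 39 per group gives 79.7% power and 40 gives 80.7%, so 40.
- With 60% retention: 40 / 0.60 = 66.7, so 67 per group and 134 in total.

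The stated 40 and 134 reproduce and are not in question. They supply the two arm sizes used below: 67 if missing outcomes are filled in by last observation carried forward, and 40 if only retained participants are analysed.

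**Inputs that are assumptions.** The documents give none of these:

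- correlation of motivation with outcome: 0.3 or 0.5;
- correlation of motivation with participation: 0.7;
- share of the intervention arm filtered out, f: 30% or 50%;
- no true treatment effect, outcome SD of 1, normal variables.

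**Bias against all controls.** Participation and outcome then correlate at rho = 0.3 × 0.7 = 0.21 or 0.5 × 0.7 = 0.35. If the top share q = 1 − f is kept, the expected spurious benefit is rho × φ(z) / q, where z is the normal quantile at f. φ(z) is 0.3477 for f = 30% and 0.3989 for f = 50%.

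- rho 0.21, f 30%: 0.21 × 0.3477 / 0.70 = 0.10 SD
- rho 0.21, f 50%: 0.21 × 0.3989 / 0.50 = 0.17 SD
- rho 0.35, f 30%: 0.35 × 0.3477 / 0.70 = 0.17 SD
- rho 0.35, f 50%: 0.35 × 0.3989 / 0.50 = 0.28 SD

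**False-positive rate.** This comes from simulation (40,000 null trials per setting), using a two-sided t test at 0.05 of the kept participants against all controls:

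| rho | Filtered | Bias (SD) | 67 per arm | 40 per arm |
|---|---|---|---|---|
| 0.21 | 30% | 0.10 | 8.5% | 7.3% |
| 0.21 | 50% | 0.17 | 12.1% | 9.3% |
| 0.35 | 30% | 0.17 | 14.6% | 10.6% |
| 0.35 | 50% | 0.28 | 25.4% | 17.0% |

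Separate runs at 67 per arm gave 8.9, 12.9, 14.7 and 24.9%, which agrees within simulation error.

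**Sensitivity to the correlation.** With 67 per arm and 60% kept, a direct participation-outcome correlation of 0 gives no bias and 5% rejections. A correlation of 0.1 gives 0.06 SD and 6%. A correlation of 0.5 gives 0.32 SD and 38%.

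**If the comparison is within the intervention arm.** Under the null the arm's overall mean is zero, so high minus low participators equals the bias above divided by f. That gives 0.104 / 0.30 = 0.35, 0.168 / 0.50 = 0.34, 0.174 / 0.30 = 0.58 and 0.279 / 0.50 = 0.56 SD. Changing the comparator does not remove the problem.

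**The case against.** Several points on the other side stand.

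- **Comparator.** A reader might infer that the plan states a comparison of motivated participants with all controls. It does not, because no comparator is named. All controls is the natural reading, since no control subset is described, but the table applies only to that reading.
- **Certainty and direction.** A reader might also infer that a false benefit is bound to appear. The documents do not support that. The bias needs a positive link between participation and reduced use. Without a link it is zero, and if heavier or more distressed users reply more, it could run the other way.
- **Size.** The correlations and filter shares are assumed. The upper figure of about 25% holds only with 67 analysed per arm; at the 40 expected to be retained it is about 17%.
- **Stakes.** This is a supplementary analysis in the Discussion of a condensed article. The planned analyses are intention-to-treat, and nothing ties the implementation decision to the filtered result. The full protocol may give more detail.
- **Remedy.** A complier-average effect needs allocation to act only through participation above the threshold. Under the Intervention group section, counsellors contact participants at least twice a week, so silent participants still receive messages and may benefit. Suppose that 50% pass the threshold with a true effect of 0.30 SD and the rest get half of that. The intention-to-treat effect is 0.5 × 0.30 + 0.5 × 0.15 = 0.225, and the estimate is 0.225 / 0.5 = 0.45 SD, which is inflated.

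None of this rescues the label. Under either comparator the contrast is self-selected, and the one matching procedure described neither covers this analysis nor includes motivation. Further detail elsewhere would not make the stated filter a randomised comparison.

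**Conclusion.** The point holds in conditional form. The filter conditions on a post-randomisation choice described for one arm only, so its result is not a randomised estimate and should not be called the actual effect. A benefit can appear without a true effect if participation is positively related to reduced use. Under the assumed inputs and the all-controls reading, this is about 0.10 to 0.28 SD, or up to 0.28 / 0.64 = 44% of the effect size used for planning. The false-positive rate is about 9 to 25% at 67 per arm or 7 to 17% at 40. These figures show scale and do not forecast this trial. The intention-to-treat primary analysis and the sample size are unaffected. The change should be made, but it does not threaten the trial's main conclusion.

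**What to change.** 1. Remove the causal label from the sentence in the Discussion. Describe any filtered result as exploratory and non-randomised, and name its comparator.
2. If a causal estimate of participation is wanted, keep all 134 participants as randomised and estimate a complier-average effect with allocation as the instrument (for example, two-stage least squares). Fix a low participation threshold in advance, such as any reply, and include baseline covariates, among them contemplation stage and treatment motivation. As described, controls have no access to the counselling chat, so non-adherence is one-sided.
3. State the exclusion restriction and add a sensitivity analysis that lets participants below the threshold receive part of the benefit, because messages they read without replying would inflate the estimate.

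The change affects analysis wording only and needs no new data. The price is one assumption to defend and a wider interval. At 67 per arm, without covariates, the filtered contrast has a standard error of about √(1/67 + 1/47) = 0.19 SD with 30% filtered and √(1/67 + 1/34) = 0.21 SD with 50%. The complier-average estimate has about √(2/67) / 0.7 = 0.25 and √(2/67) / 0.5 = 0.35 SD. A low threshold that more participants pass narrows this gap. Step 1 alone is the minimum and costs nothing.
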